# Effect of different rehabilitation training timelines to prevent shoulder dysfunction among postoperative breast cancer patients: study protocol for a randomized controlled trial

**DOI:** 10.1186/s13063-020-04954-3

**Published:** 2021-01-06

**Keywords:** Rehabilitation training, Shoulder dysfunction problems, Timeline, Breast cancer, Randomized controlled trial

## Abstract

**Introduction:**

Due to advancements in treatment, the survival of breast cancer (BC) patients has significantly improved. Improving the postoperative quality of life has become a widespread concern for patients and doctors. At present, the staged rehabilitation training program for postoperative BC patients has been recognized. However, there is not yet a consensus about the optimal time to initiate rehabilitation training. We designed this study to investigate the optimal intervention times for postoperative BC patients to begin different stages of rehabilitation.

**Design:**

This is a randomized controlled trial. Female participants with BC who are scheduled to undergo mastectomy, including unilateral total breast or breast-conserving surgery plus axillary lymph node dissection, will be enrolled in this study. The intervention includes the following: 200 participants will be allocated using a 1:1:1:1 ratio to the A, B, C, and D groups, which have four different rehabilitation timelines for four phases of rehabilitation exercises. A therapist will evaluate the patient’s overall health and then adjust the training intensity before initiating training. The assessments include upper limb mobility, grip, limb circumference, postoperative drainage volume (PDV), and pain. The training will last for 12 weeks, and patients will undergo follow-up twice within 6 weeks after discharge. Outcomes include the following: Constant-Murley Score (CMS) is the primary parameter. European Organization Research and Treatment of Cancer Quality of Life Questionnaire-BR23 (EORTC QLQ-BR23), SF-36, range of motion (ROM), strength, grip, circumference, PDV, and pain are the secondary parameters. All enrolled subjects will be assessed at 1 day, 3 days, 1 week, and 2, 3, 6, 9, 12, and 18 weeks after the surgery.

**Discussion:**

This is a randomized controlled trial to evaluate the effect of different rehabilitation training timelines to prevent shoulder dysfunction among postoperative patients with BC. If the results are confirmed, this study will establish an optimal timeline for postoperative BC rehabilitation.

**Trial registration:**

ClinicalTrials.gov NCT03658265. Registered on September 2018.

## Introduction

Breast cancer (BC) is the most commonly diagnosed malignant tumor among women worldwide. According to the statistics in America in 2018, BC alone accounted for 30% of all new cancer diagnoses in women [1]. Although China has a relatively low incidence of BC compared to America, it has increased by 20–30% in the past few decades and is growing by 3–5% annually according to the National Central Cancer Registry of China [2, 3]. Previously, the most common cause of cancer death in women age 20–59 years was BC [4]. However, early detection and surgical intervention have continued to improve, and BC survival rates now reach 90% [1].

BC treatment mainly involves surgery, along with radiotherapy and chemotherapy. The most common surgical procedures are sentinel lymph node biopsy (SLNB) and axillary lymph node dissection (ALND) for the lymph nodes [5], which are usually combined in clinical practice. SLNB is a less invasive method of evaluating nodal involvement in order to detect metastasis in a lymph node. Women with affected sentinel lymph nodes should be offered ALND [6, 7]. A meta-analysis has shown no differences between SLNB and ALND in overall survival, disease-free survival, or regional lymph node recurrence; however, it has shown significant differences in postoperative morbidity and quality of life [8]. ALND, also known as modified radical mastectomy, is indicated in patients who present with axillary metastases that are palpable or diagnosed via needle biopsy [9]. Surgery generally resects the mammary gland and the fascia of the pectoralis major and the latissimus dorsi, retaining both the pectoralis major and the pectoralis minor. During this procedure, there is a high risk of injury to the related muscles and nerves. In addition, the axillary lymph nodes and the lymphatic adipose tissue of the subscapular area are removed. After suturing and compression dressing, tissue around the armpit adheres to the muscles, forming a stiff and inelastic scar tissue, which affects upper limb mobility. Surgery combined with chemotherapy and radiotherapy may also disrupt the lymphatic reflux, which can lead to lymphedema and limit physical activity. Long-term reduced shoulder function causes chronic pain, muscle atrophy, decreased strength, decreased mobility, upper limb edema, sensory disturbance, and decreased cardiopulmonary endurance, which can severely affect patient’s emotions and quality of life [10, 11].

A meta-analysis of randomized controlled trials has shown that postoperative physical therapy has beneficial effects on BC sequelae and thus can improve shoulder function, reduce lymphedema risk, and improve the quality of life [12]. Among all kinds of therapy modalities [13–15], active exercises and stretching have been proven to be much more effective in the treatment of upper limb dysfunction than other modalities [16, 17], and accordingly, active exercises and stretching are recommended by clinical guidelines [18]. Active exercises have important physiological benefits in maintaining the blood and lymphatic flow to joints and soft tissues, which can prevent the shortening and weakness of the surrounding muscles and connective tissues that may occur following immobilization after surgery [15, 19]. At present, stretching is the widely used treatment for shoulder dysfunction after BC [16, 17]. Continuous stretching prevents contracture, tension, and adhesion of the pectoral muscles [20]. Furthermore, stretching involves the execution of movement patterns throughout the available ROM, which can improve joint mobility, enhance muscle strength, and provide a good foundation for further exercise to achieve good results [21, 22].

However, the optimal timeline for initiating postoperative rehabilitation for BC patients is not yet clear. There are many related clinical studies, and the timing in these studies ranged from postoperative 1 day to 1 year [16]. Currently, it is commonly thought that early institution of flexion and abduction exercises following axillary dissection appears to have a harmful effect on PDV and wound healing. Adequate functional ROM is attained in all patients with minimal complications when active motion exercises are delayed for up to 7 days after axillary dissection [23]. A meta-analysis has shown that researchers are more inclined to start rehabilitation exercises early. Early and delayed exercises have not been found to cause significant differences in the incidences of delayed wound healing, wound aspiration, pain, or lymphedema [16]. Therefore, we speculate that early rehabilitation is feasible for postoperative patients. We aim to investigate the effect of different timelines of multifactorial physical therapy in postoperative BC patients.

### Aim of this study

The aims of this study are as follows:
Observation of the optimal active exercises of the shoulder joint under full evaluation at 3 days after surgery, with respect to whether it accelerates the recovery of shoulder function and improves the quality of life of postoperative patients with BC. Evaluation of whether early-stage rehabilitation training leads to an increase in PDV, which affects shoulder function and the time of extubation in BC patients.Observation of progressive resistance training (PRT) in the case of full evaluation at 3 weeks after surgery, with respect to whether it promotes the recovery of shoulder function.

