Upper limb mobility is mainly reflected in both ROM and muscle strength. A medical protractor is usually used to assess the range of shoulder motion and follow standardized measurement principles to reduce compensatory motion. Passive flexion and abduction of the shoulder will be assessed in a supine position with gravity as a standard resistance. Active flexion and abduction will be assessed in a sitting position. Manual muscle test (MMT) and dynamometer are generally used to measure the maximum strength of the shoulder muscles. Strength evaluation will require the patients to take the supine position in the early stage and then gradually change to the sitting position in the late stage. The arms will be fixed at 90° to assess flexion and abduction muscle strength. The patient will be asked to perform three maximum voluntary contractions in each direction, recording the highest data from three attempts. Each arm will be measured separately. The most common method to determine whether the upper extremity has edema is the measurement of upper limb circumference. Using the antecubital fossa and palm as location points, the circumferences of the bilateral arms in a specific position will be measured, and the differences will be compared between the two sides. If the difference between the two sides is greater than 2 cm at the same site, it will indicate edema. PDV and pain will be assessed through consultation. PDV will be recorded by the nurse and will be uploaded to the hospital work system regularly. The therapist will ask the nurse about PDV and pain or directly search the system. Daily pain or pain at the end of the active/passive range of each exercise will be measured clinically using a standardized 10-cm visual analog scale (VAS). VAS is widely used clinically to assess postoperative pain and to monitor the effectiveness of treatment. VAS is based on self-reporting via a unidimensional scale that aims to represent subjective pain intensity [25, 26].

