#### Secondary parameters

Quality of life (QOL) is a multidimensional, subjective construct that reflects physical, mental, and social health domains of patients [32]. The European Organization Research and Treatment of Cancer (EORTC) QLQ-BR23 questionnaire is one of the most available tools for assessing aspects of QOL for BC patients [33]. It contains 23 items divided into two functional scales, including body image and sexuality, and three symptom scales, including arm symptoms, breast symptoms, and systemic therapy side effects. This questionnaire has been found to have a high internal consistency for 4 out of 5 scales and well-known group discriminative ability [34]. The validity of the EORTC QLQ-BR23 has been internationally scrutinized and explored in many countries, which has ultimately confirmed the questionnaire’s validity in BC [35].

The SF-36 is a general brief self-report questionnaire that assesses health-related QOL. The SF-36 contains 36 items that measure eight multi-item variables, including physical functioning, social functioning, role limitations due to physical problems, role limitations due to emotional problems, mental health, energy and vitality, bodily pain, and general perception of health, and there is a single-item scale on health transition. The score of each item ranges from 0 to 100. For each variable, the item scores are calculated, and a higher score indicates a better health status [36]. The internal consistency of the variables in the SF-36 is assessed with Cronbach’s α statistic and test-retest reliability [37]. Studies have shown that the SF-36 is acceptable for patients, and it has a high level of internal validity and good test-retest properties [38].

The assessments of shoulder function and quality of life will be evaluated at 1 week, 3 weeks, and 9 weeks after surgery.

In addition, joint mobility, muscle strength, grip, circumference, PDV, and pain, the parameters of exercise intensity in the pre-assessment, will also be evaluated as outcomes. Assessment methods and principles are the same as those for pre-assessments.

Shoulder ROM and strength will be assessed at postoperative 3 days and 1, 2, 3, 6, and 9 weeks. Grip will be evaluated at postoperative 1 day, 3 days, and 1, 2, 3, and 6 weeks, and upper limb circumference will be assessed at postoperative 1 day and 3, 12, and 18 weeks. PDV, pain, and skin will be evaluated by interview and palpation at postoperative 1 day, 3 days, 1 week, and 2 weeks.

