### Statistical analyses

Analyses will be performed using SPSS statistical software (version 20.0) by a statistician in the Department of Rehabilitation Medicine, Zhongnan Hospital of Wuhan University. Data will be analyzed according to the “intention-to-treat” (ITT) principle. A two-sided significance level of 5% will be used for all analyses. If the experimental data satisfies the normal distribution and the homogeneity of the variance, one-way analysis of variance (ANOVA) will be performed for comparison among the 4 groups with respect to the CMS, EORTC QLQ-BR23, SF-36, ROM, strength, grip, circumference, PDV, and pain. If there is an overall difference, the Tukey method for multiple comparisons will be used to compare the differences between groups at each time point. The results of repeated measurement ANOVA testing at each time point in each group will be analyzed by repeated measures to observe the recovery of patients at different times after surgery. For data with irregular variance, variable transformation can be used after the Kruskal-Wallis *H* test.

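### Aim 2 refers to time of extubation, but drain removal is not an outcome, and drainage is compared only visit by visit, with two visits after the groups diverge

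*Protocol article*

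**What the plan says.** The second aim (Protocol article, Aim of this study) is to evaluate whether early-stage training "leads to an increase in PDV, which affects shoulder function and the time of extubation in BC patients".

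The outcomes are named in three places, and each includes postoperative drainage volume (PDV) but not extubation or drain removal:
- Abstract, Design: "SF-36, range of motion (ROM), strength, grip, circumference, PDV, and pain are the secondary parameters".
- Secondary parameters: "joint mobility, muscle strength, grip, circumference, PDV, and pain, the parameters of exercise intensity in the pre-assessment, will also be evaluated as outcomes".
- Statistical analyses, where one-way ANOVA compares the four groups "with respect to the CMS, EORTC QLQ-BR23, SF-36, ROM, strength, grip, circumference, PDV, and pain".

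The schedule under Secondary parameters is: "PDV, pain, and skin will be evaluated by interview and palpation at postoperative 1 day, 3 days, 1 week, and 2 weeks". After an overall difference, "the Tukey method for multiple comparisons will be used to compare the differences between groups at each time point".

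Under Training timelines, groups C and D start phase 2 on day 3, and groups A and B start it at 1 week. Phase 4 starts in the third week (B, D) or the fourth (A, C).

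On the source data, Assessment for training says that "PDV will be recorded by the nurse and will be uploaded to the hospital work system regularly".

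**The concern.** The Introduction reports the common view that early flexion and abduction exercise after axillary dissection harms drainage and wound healing. Phase 2 consists of flexion and abduction work, and two of the four groups receive it earlier. Drainage is therefore a central question about the early timelines, and the aims say so.

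Two things stand between that aim and an answer. First, the extubation part has no matching variable. Second, volume at fixed visits is an awkward measure of drainage, because a patient whose drain is out no longer produces a reading. If such patients drop out of the comparison, the groups are compared on a subset formed after randomisation by the quantity under study. A real increase would then look smaller than it is.

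**Working it through.** **1. Aim against outcomes.** The primary parameter is the Constant-Murley Score. The secondary parameters, their schedule, the 12- and 18-week follow-up data and the analysed variables contain no extubation or drain-removal time. The only other mention of drain removal is in the Discussion, in a guideline summary about stretching. Figures 1 and 2 could not be checked, so this rests on the text.

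**2. What each PDV visit can show.**

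| Visit | Phase 2 in C, D | Phase 2 in A, B | Bearing on aim 2 |
|---|---|---|---|
| Day 1 | not started | not started | baseline |
| Day 3 | starting | not started | at the point of divergence |
| Week 1 | under way since day 3 | just due | contrast present |
| Week 2 | under way | under way since week 1 | contrast of timelines |

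Two of the four visits inform the aim. Up to week 2, A and B have the same planned training, and so do C and D, because phase 4 has not begun. Of the 4 × 3 / 2 = 6 Tukey pairs, four (A–C, A–D, B–C, B–D) carry the early-versus-later contrast. The other two carry no drainage question.

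**3. Size of the selection, if it occurs.** The article gives no drainage figures to reproduce, so every input here is an assumption. Daily output on day t was taken as

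ln(output) = ln(150) + u − 0.09(t − 1) + e + ε,

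with between-patient u of SD 0.5 and within-patient ε of SD 0.3. The early-training effect e was ln(1.20) or ln(1.40) at both visits, and 0 for the later groups. A drain counted as out at week 1 if day-6 output was below a cut-off, and at week 2 if day-6 or day-13 output was below it. Output after removal was missing. The cut-offs of 20, 30 and 50 mL only span a range and are not proposed rules.

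Ratios of mean output, early to later, among patients still drained:

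| Cut-off | Week 1, true 1.20 | Week 2, true 1.20 | Week 2, true 1.40 | Still drained at week 2, later / early (true 1.20) |
|---|---|---|---|---|
| 20 mL | 1.198 | 1.180 | 1.365 | 94% / 97% |
| 30 mL | 1.187 | 1.152 | 1.315 | 81% / 89% |
| 50 mL | 1.162 | 1.115 | 1.233 | 51% / 63% |

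Share of the log effect lost for a true 1.20, as 1 − ln(observed)/ln(1.20):
- Week 2, 20 mL: 1 − 0.1655/0.1823 = 9%.
- Week 2, 50 mL: 1 − 0.1089/0.1823 = 40%.
- Week 1, 50 mL: 1 − 0.1501/0.1823 = 18%.

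With no true effect the ratio stayed at 1.00 for every cut-off. The last column shows that a rise in drainage would also appear as later drain removal, which the plan does not capture.

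**The case against.** **The wording of the aim.** The clause on shoulder function and extubation can be read as explaining why PDV matters, not as naming a second endpoint. That reading is possible, and it makes this a modest mismatch. Even so, the article ties PDV to extubation time and then gives no means of examining the link.

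**The selection.** A reader might infer that the later comparisons are in fact restricted to high-output patients. The document does not support that. It gives no removal rule, no expected drain duration and no coding of PDV after removal, and coding is commonly left to a fuller plan. If volume after removal is entered as zero, this selection does not arise. The article also does not say whether PDV at a visit is a daily or a running total.

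**The size.** A reader might also put the loss above half. With log-normal output (log SD 0.5), a true ratio of 1.30 and removal below the control median of the same measurement, the log means among those still drained are 0.399 and 0.510. The difference is 0.111 against a true 0.262, a ratio of 1.12, so 1 − 0.111/0.262 = 58% is lost. The arithmetic is right, but half the control drains are out and removal is decided by the very value being compared. It exceeds the 9% to 40% found at week 2 for a true ratio of 1.20.

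**The visits.** Week 2 should not be dismissed because A and B have started phase 2. The randomised comparison is of timelines, so week 2 remains valid. Nor is sparse sampling a fault of the source data, since nurses record PDV regularly. The limit lies in the outcome schedule.

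**Conclusion.** The point holds in a limited form. As written, the plan leaves the extubation part of aim 2 unanswered, and it measures drainage by visit only, with two visits after the groups diverge.

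The selection effect is conditional. It needs removal on low output, removal before the visit, and later values treated as missing. Under those assumptions a true ratio of 1.20 reads as about 1.12 to 1.18 at week 2 and 1.16 to 1.20 at week 1. The simulation checks the cut-off only on the day before each visit and holds the effect constant to week 2, so these figures show direction and rough size only.

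A reader might conclude that the plan is biased towards finding no increase in drainage. That goes too far: the effect is attenuation of a real increase, it vanishes when there is none, and nothing in the article says that a non-significant ANOVA will be taken as proof of no increase. The primary outcome is unaffected.

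**What to change.** Add two secondary outcomes for aim 2, for every randomised patient, from the nursing record already kept:
- days from surgery to drain removal;
- cumulative drainage volume from day 3 to removal.

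Both are defined whether or not a drain is still in at a given visit. Removal is simply recorded as it happens, and no clinical rule changes.

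Compare C+D (phase 2 at day 3) with A+B (phase 2 at week 1), planned as 2 × 50 = 100 patients each. Adjust volume for day-1 PDV, and report each difference with a 95% confidence interval. The by-visit PDV table can stay as description, with a sentence on how values after removal are handled, but the aim 2 conclusion should not rest on patients still drained.

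Recruitment was planned to end in May 2020, so the addition should be dated and made before the analyst sees results by group.

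The cost is extra data extraction and analysis work, with no new visit or procedure. Volumes may need collecting separately for any patient discharged with a drain in place; the article does not say whether this happens.

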## Methods and design

### Study setting and design

This is a randomized controlled clinical trial, which is currently being conducted at the Department of Rehabilitation Medicine, Zhongnan Hospital of Wuhan University. The study protocol was approved by the Medical Ethics Committee of Zhongnan Hospital of Wuhan University in September 2018. We have registered the trial content with ClinicalTrials.gov (www.clinicaltrials.gov), which is a publicly accessible primary registration authority that participated in the WHO International Clinical Trial Registry Platform (Registration time: September 2018, No. NCT03658265). The authors confirm that all ongoing and related trials are registered. All methods used in this protocol will be performed in accordance with the Standard Protocol Items: Recommendations for Interventional Trials (SPIRIT) [24].

Subjects were patients who will be recruited from the Department of Thyroid and Breast Surgery of the Zhongnan Hospital of Wuhan University from September 10, 2018, to May 31, 2020. According to the patient’s operation time sequence, we will enroll 200 patients in the trial, number them, and randomly divide them into four groups. Subjects will be asked to provide written informed consent. Subjects will perform different rehabilitation exercises at different times, and they will receive assessments from relevant physiotherapists regularly. The flowchart of this study is presented in Fig. 1.

**Fig. 1 Fig1:**
[figure not shown]
Flowchart of this study

### Participant recruitment—inclusion criteria/exclusion criteria

#### Inclusion criteria

Women will be eligible to enroll in the trial if they meet the following criteria:

(a) Between the ages of 25 and 75 years; (b) pathological diagnosis of BC; (c) patients undergoing mastectomy including unilateral total breast or breast-conserving surgery, with a positive SLNB result, for whom affected axillary lymph nodes have been removed; (d) postoperative chemotherapy or radiation therapy according to the condition; (e) no other malignant tumors within 5 years; (f) no physical therapy-related contraindications; and (g) willingness to sign the informed consent form.

